# IMPOSE (IMProving Outcomes after Sepsis)—the effect of a multidisciplinary follow-up service on health-related quality of life in patients postsepsis syndromes—a double-blinded randomised controlled trial: protocol

**DOI:** 10.1136/bmjopen-2014-004966

**Published:** 2014-05-24

**Keywords:** Rehabilitation Medicine

## Abstract

**Introduction:**

Patients post sepsis syndromes have a poor quality of life and a high rate of recurring illness or mortality. Follow-up clinics have been instituted for patients postgeneral intensive care but evidence is sparse, and there has been no clinic specifically for survivors of sepsis. The aim of this trial is to investigate if targeted screening and appropriate intervention to these patients can result in an improved quality of life (Short Form 36 health survey (SF36V.2)), decreased mortality in the first 12 months, decreased readmission to hospital and/or decreased use of health resources.

**Methods and analysis:**

204 patients postsepsis syndromes will be randomised to one of the two groups. The intervention group will attend an outpatient clinic two monthly for 6 months and receive screening and targeted intervention. The usual care group will remain under the care of their physician. To analyse the results, a baseline comparison will be carried out between each group. Generalised estimating equations will compare the SF36 domain scores between groups and across time points. Mortality will be compared between groups using a Cox proportional hazards (time until death) analysis. Time to first readmission will be compared between groups by a survival analysis. Healthcare costs will be compared between groups using a generalised linear model. Economic (health resource) evaluation will be a within-trial incremental cost utility analysis with a societal perspective.

**Ethics and dissemination:**

Ethical approval has been granted by the Royal Brisbane and Women’s Hospital Human Research Ethics Committee (HREC; HREC/13/QRBW/17), The University of Queensland HREC (2013000543), Griffith University (RHS/08/14/HREC) and the Australian Government Department of Health (26/2013). The results of this study will be submitted to peer-reviewed intensive care journals and presented at national and international intensive care and/or rehabilitation conferences.

**Trial registration number:**

Australian and New Zealand Clinical Trials Registry ACTRN12613000528752.

Strengths and limitations of this study
This is the first study to concentrate solely on patients with sepsis syndrome postintensive care discharge.There is a strong multidisciplinary team to provide a multitude of screening tools and interventions.Individualised management will be provided to patients.This is a single-centre study, so lacks external generalisibility.

## Background

Greater numbers of patients are surviving in intensive care units (ICUs) but a new syndrome called the ‘post-ICU syndrome’ has appeared with residual physical, cognitive and psychosocial problems lasting from 5 to 15 years.^1^
^2^ The rate of a major illness recurring and/or mortality is also increased in the year after ICU discharge, with mortality ranging from 26% to 63% at 1-year postdischarge in long-stay ICU patients (≥48 h).^3^ ICU survivors additionally often have a number of problems^1–4^ including debility and fatigue from loss of muscle mass, ongoing nutritional problems, difficulty in dealing with altered appearance and function, chronic pain,^5^ amnesia and delusional symptoms. All of these factors have a major impact on the health and productivity of survivors and their carers, survivors’ return to work rates, as well as the impact on availability of ICU and hospital beds, surgical waiting lists, health costs and society.^6^ There has been a ‘call to arms’ to provide improved management regimes to ICU survivors.^7^ The National Institute of Health and Care Excellence (NICE) clinical guidelines^8^ provided by the National Health Service (NHS) NICE recommend ‘optimisation of recovery’ rather than merely survival post-ICU. All of these problems are particularly present in survivors of sepsis.^9^

Sepsis is defined as a powerful inflammatory response to severe infection.^10^ The annual total cost of sepsis syndromes in the USA is $16.7 billion nationally^11^ with the incidence projected to increase by 1.5% per annum as patients develop more comorbidities and resistant organisms. In brief, sepsis is a major public health concern.^12^

However, the statistics above do not include the cost of ongoing disability and loss of productivity postillness. Patients with sepsis syndromes have significantly worse outcomes with lower health-related quality of life (HRQoL),^13–16^ particularly in the physical domain,^17^
^18^ chronic pain^5^
^19^ and cognitive domain^20^ compared with non-septic ICU survivors. While other critically ill/injured or disabled patients, for example, those with burns, strokes, head injuries have established follow-up regimes, patients with sepsis are not referred to formal rehabilitation and are discharged home with extremely poor function.

Follow-up ICU outpatient clinics are a recent innovation particularly within the UK.^21–23^ These clinics identify and provide intervention for problems posthospital discharge including weakness, poor balance, impaired swallowing and nutrition, ongoing emotional problems and/or post-traumatic stress disorder in critical illness survivors. The one completed clinical trial on this topic^24^ did not find a significant improvement in HRQoL. Researchers admitted that one discipline was not ideal and ‘further work should focus on the roles of early physical rehabilitation, delirium, cognitive dysfunction and relatives’. The programme was conducted in a generic group of ICU survivors including those with only an overnight stay, and there may be greater discriminatory power in selecting only one diagnostic group with a documented poor outcome such as sepsis syndrome. Additionally some countries (Canada, Australia, South Africa) have major problems with large land area and relatively sparse population in rural areas leading to a lack of resources and problems with follow-up post-ICU.^25^

## Aims

The primary aim of this research is to investigate whether targeted follow-up and intervention will improve HRQoL in survivors of sepsis syndromes. Secondary aims will be to investigate whether this intervention decreases readmission rates to hospital, 12-month mortality and health resource use.

This project will be an important investigation of follow-up and management of ICU patients in a subpopulation (sepsis) documented to have poor outcomes.^16^ The project will incorporate a subgroup (rural patients) via telemedicine^26^ in a novel method to overcome the problem of the ‘tyranny of distance’ in follow-up.

### Hypotheses

The hypotheses are that posthospital follow-up will improve HRQoL, decrease mortality, economic and health resource use and readmission to hospital in patients postadmission to ICU with sepsis syndrome.

## Methods/design

This is a prospective, double-blinded, interventional, repeated measures, superiority, randomised controlled trial with concealed allocation, blinded assessors and intention-to-treat analysis. The study has been designed in accordance with the Consolidated Standards for Reporting of Trials guidelines^27^ (figure 1) and the Standard Protocol items: Recommendation for Interventional Trials (SPIRIT 2013).^28^ The trial will be completed in two outpatient clinics. One clinic will be in the outpatient department located at the university-affiliated tertiary hospital Royal Brisbane and Women’s Hospital (RBWH), Brisbane, Australia; the other will be located at a regional hospital—the Bundaberg Base Hospital, Bundaberg, Queensland, Australia.

**Figure 1 BMJOPEN2014004966F1:**
[figure not shown]
CONSORT flow diagram.

### Participants

Participants will be recruited from among patients being discharged from a quaternary university-affiliated ICU at RBWH, Brisbane, Australia. Participants will be randomised to one of the two groups (intervention or control) post-ICU discharge and just prior to discharge from hospital.

#### Inclusion criteria

Patients included will be men or women ≥18 years of age, with a documented episode(s) of sepsis^10^ (≥2 criteria of a systemic inflammatory response plus proven or strongly suspected infection, severe sepsis defined as sepsis plus organ failure, septic shock defined as severe sepsis not responding to management) and required respiratory support for longer than 48 h. Enrolment in the study should be within 1 month of discharge from hospital.

#### Exclusion criteria

Patients with neurological injuries, spinal injuries and burns will be excluded, as these patients have existing rehabilitation programmes and community support groups. Patients with haematological conditions or requiring palliative care post-ICU will also be excluded. Patients with psychiatric and/or mental disabilities that preclude them from understanding the questionnaires and non-English speaking patients will also be excluded.

### Randomisation

Participants will be randomised by opaque sealed envelopes after enrolment. Numbers on the envelopes will be generated by a computer-generated randomisation (http://www.randomization.com) table based on blocks of four to assign patients to either the intervention or the usual care group. The randomisation sequence will be concealed from consent designee staff and protected by an electronic password. Participants will be stratified based on a score >3 on the Cumulative Illness Rating Scale (CIRS-G).^29^

We are stratifying patients as most patients who develop sepsis syndromes have a number of comorbidities, but there can be a small number of relatively young, healthy patients who are affected. The allocation sequence will be generated by the research assistant attached to the trial. Patients will be consented by the chief investigator ([name]) and assigned to interventions by a second investigator (PT).

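### A single, published block size of four makes up to a third of allocations deducible in the worst case; undisclosed, randomly varying block sizes would remove most of that certainty at little cost

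*Protocol article*

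**What the plan says.** The Randomisation section of the protocol article specifies a computer-generated "table based on blocks of four to assign patients to either the intervention or the usual care group". It mentions no other block size and does not say that the size is withheld from anyone. Stratification is by one factor, a CIRS-G score above 3 or not.

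The same section sets out the safeguards. "Participants will be randomised by opaque sealed envelopes after enrolment". The list is password-protected and hidden from the staff who take consent. Three roles are separated: "The allocation sequence will be generated by the research assistant attached to the trial", the chief investigator takes consent, and a second investigator assigns patients to their arm.

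Methods/design describes the study as a "randomised controlled trial with concealed allocation, blinded assessors and intention-to-treat analysis", and the section on protecting against other sources of bias repeats the claim of concealment. That section lists as blinded the assessors, the data analysts and some of the investigators. The assigning investigator is not on the list.

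On setting, the Participants section states: "Participants will be recruited from among patients being discharged from a quaternary university-affiliated ICU at RBWH, Brisbane, Australia". The strengths and limitations list calls the trial single-centre. Under Intervention, only one arm attends the trial's follow-up clinic; the other has usual care.

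**The concern.** Hiding the list and preventing prediction are separate tasks. Envelopes and a password do the first. With a known, fixed block size, anyone who can see how the current block has gone so far can sometimes work out the next allocation without seeing the list.

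Several features of this trial make that easier than usual. One ICU supplies all patients, so one team could see most of the sequence. There are only two strata to follow. The arms cannot be disguised from the staff who deliver or arrange care, and the assigning investigator must learn each allocation.

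If a person who approaches or consents patients could predict the next arm, the prediction might influence, even unconsciously, who is approached and when. The eligibility criteria leave some room for this: enrolment is tied to a window of one month around discharge, and some exclusions call for judgement. The result would be selection bias in a trial whose primary outcome is self-reported quality of life. Adjustment for baseline measures would deal with the measured part of such an imbalance but not the unmeasured part.

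**Working it through.** **Inputs.** Block size four (Randomisation). Total of 204 patients (Sample size). Two strata (Randomisation). The 1:1 ratio is not stated outright; it is inferred from the two equal groups of 78 in the Sample size section. The share of patients in each stratum is not given, so a range of 50% to 90% in one stratum is assumed.

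**The plan's own figures.** The article gives no figure for predictability. Its 78 per group does reproduce under 1:1 allocation: 2 × (15 × (1.960 + 1.282) / 7.8)² = 77.7, rounded up to 78. The total of 204 is taken as stated.

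**Certain allocations in a block of four.** There are 6 equally likely arrangements of two A and two B.
- In AABB and BBAA (2 of 6), the last two allocations are certain from the earlier ones.
- In the other 4 of 6, only the last is certain.
- Expected number certain per block: (2 × 2 + 4 × 1) / 6 = 1.333.
- Share: 1.333 / 4 = 33.3%. Over 204 / 4 = 51 blocks this is 51 × 1.333 = 68 patients.

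**Best-guess accuracy in a block of four.** The chance of a correct guess at positions 1 to 4 is 1/2, 2/3, 2/3 and 1. The sum is 2.833, and 2.833 / 4 = 70.8%, against 50% by chance.

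**Two strata and incomplete final blocks** (simulation, 204 patients, stratum share 50% to 90%). An observer who tracks the strata has 32.9% to 33.0% certain, about 67 of 204. An observer who ignores the strata is certain of none; what look like deductions are right 61% to 68% of the time.

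**Other block schemes.** For one known block size of 2b, the certain share is 1/(b + 1). For mixed sizes the figures come from simulating a single list of 204 with sizes equally likely. The observer knows the set of sizes and all earlier allocations, but not the order of the sizes.

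| Scheme | Certain | Best guess correct |
|---|---|---|
| Fixed 4 | 33.3% | 70.8% |
| Fixed 6 | 25% | 68.3% |
| Fixed 8 | 20% | 66.6% |
| Random 4, 6 | about 5.5% | about 69% |
| Random 4, 6, 8 | about 2.3% | about 68% |

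On 204 patients, 5.5% is about 11 and 2.3% is about 5. Varying the sizes removes nearly all the certainty, but only two or three percentage points of best-guess accuracy.

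**Price in balance.** An unfinished final block can leave a stratum uneven by at most half the block: 2 patients with size 4, and 4 patients with size 8.

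**The case against.** The strongest reply is that the person who would have to act on a prediction may have nothing to predict from. Consent and assignment are done by different investigators, envelopes are used after enrolment, and the list is hidden from consenting staff. Nothing in the article shows that the consenting investigator learns past assignments. That person's name is removed, so it cannot be checked against the blinded investigators. This stands, and it is why the 33% is a ceiling and not an expected rate.

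The route by which staff would learn allocations is also not described. Clinic attendance alone would be a slow signal. If 204 patients were recruited over the 2 years mentioned under Contingencies, that is 204 / 24 = 8.5 a month. If a first visit came about two months after discharge (an assumption), about 17 patients, or some four blocks, would already have been randomised. Control patients may also be referred to outpatient clinics, so a referral alone does not identify the arm. This stands too. It does not cover the assigning investigator, who knows each allocation at once, or what is shared within a small team.

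A reader might go further than the text allows in four ways:
- That concealment was broken, or that 68 allocations will be known. The article shows only a route by which deduction is possible.
- That nearly all patients sit in one stratum. The article says most patients who develop sepsis have several comorbidities; it does not say that most score above 3 on CIRS-G.
- That no analysis could help. Baseline SF36 is collected and covariate-adjusted models are planned if groups differ, which deals with measured imbalance.
- That the research assistant's generating the list is itself a flaw. The Randomisation section gives that person no consenting or assigning role.

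**Conclusion.** The point holds as an inexpensive improvement to a common design choice. It is not an error or contradiction in the protocol. With a single published block size of four, up to 33% of allocations (68 of 204, or about 67 once strata and unfinished blocks are allowed for) are certain, and the best guess is right 71% of the time. These figures assume 1:1 allocation, blocks run within each CIRS-G stratum, and an observer with a part in recruitment who knows all earlier allocations in the current block and the patient's stratum. If any of that knowledge is missing, the figures are lower. The stated safeguards reduce the risk without closing this route, and the documents do not support any claim that concealment failed.

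**What to change.** For patients not yet randomised, generate a new list with randomly varying block sizes, for example 4, 6 and 8, within each CIRS-G stratum. Do not disclose the sizes to anyone who consents or treats patients. The protocol would then say only that block sizes vary at random. It would also help to state that the consenting investigator is kept unaware of earlier assignments.

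The gain is in certainty: from 33% of allocations to about 2% (about 5.5% with sizes 4 and 6), even if the set of sizes is known. Best-guess accuracy falls only from 71% to about 68%, so the change should not be presented as making allocation unpredictable.

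The cost is a new list and a new set of envelopes, plus a short amendment if recruitment has begun; the article does not say whether it has. The worst-case end-of-stratum imbalance rises from 2 to 4 patients, which is small against 204. Sample size, eligibility and analysis are not affected.

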### Subgroup—rural patients

A small number of patients (10) originally managed in the major quaternary level ICU will be discharged to a rural area. We will test the feasibility of providing follow-up care to these patients. These patients will also be randomised to either the intervention or the usual care group. The patients will be interviewed via telemedicine (videoconferencing)^26^ and a research assistant will be appointed to complete other screening tools and refer them to appropriate agencies. If specialist services are required, for example, chronic pain clinic, these may also be accessed via telemedicine.

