### Methods for protecting against other sources of bias

This study will be double blinded with the assessors, data analysts and a number of investigators (TC, FC and GM) blinded from group allocation. There will be concealed allocation of participants. Participants will be stratified for CIRS-G.^29^ Participants when being consented will be told that they will be in one of the two groups which will be followed up posthospital and they may need to attend an outpatient clinic. Patients are unaware of the usual follow-up posthospital so should not feel they are receiving an increased/decreased level of care. Both groups will be contacted by telephone for completion of HRQoL life instruments at the required stages. Participants may have varying severity of illness, lengths of stay and/or time on mechanical ventilation in ICU; however, this will be compared between groups and if unequal adjusted models using the relevant covariates will be presented as well as unadjusted comparisons.

A few participants in either group may be referred to rehabilitation by their treating physician. This will be compared between groups. A number of patients may be uncontactable for final outcome measures; however, we have had a 95% rate in the current trial at 6 months postsepsis.^41^ The GEE^46^ will allow for missing data. If patients ‘cross-over’, that is, do not receive the planned intervention, they will still be analysed with the group they originally enrolled as per intention to treat.

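### Randomisation is stratified only by CIRS-G, so the number of the 10 or so rural patients who are allocated to telemedicine follow-up is left to chance

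*Protocol article*

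**What the plan says.** Under Randomisation, the article describes a computer-generated "table based on blocks of four to assign patients to either the intervention or the usual care group" and gives one stratification factor: "Participants will be stratified based on a score >3 on the Cumulative Illness Rating Scale (CIRS-G"). The section on protecting against other sources of bias repeats it, again alone: "Participants will be stratified for CIRS-G".

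The rural subgroup has its own section. It states that "A small number of patients (10) originally managed in the major quaternary level ICU will be discharged to a rural area", and gives the purpose: "We will test the feasibility of providing follow-up care to these patients". On allocation: "These patients will also be randomised to either the intervention or the usual care group". On delivery: "The patients will be interviewed via telemedicine (videoconferencing"), with a research assistant completing the other screening tools and making referrals.

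Under Secondary outcomes, the rural patients are kept in the full analysis and their results are set against those of metropolitan patients. No section fixes, balances or sets a minimum for the number of rural patients in the intervention arm.

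**The concern.** Whether remote follow-up works can be observed only in rural patients who receive it. The screening and referral described for the rural group are components of the intervention; usual care is referral to clinics or general practitioners at discharge. With 10 rural patients, about five are expected to be allocated to telemedicine follow-up, so losing two or three more by chance matters.

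Blocking within CIRS-G strata does not prevent this, because rural patients are scattered through the same blocks as about 194 others. The rural-metropolitan comparison is exposed too: if it is meant to compare treatment effects, it needs rural patients in both arms.

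Stratification is fixed when the envelopes are prepared. A later analysis plan can adjust for an uneven split but cannot add patients to the short arm.

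**Working it through.** **Inputs from the article**
- Rural patients: 10 (Subgroup—rural patients). This is an expected number.
- Total 204; 78 per group before allowance for loss; difference 7.8 points, SD 15, two-sided 5% level, 90% power (Sample size).
- Blocks of four, two arms, CIRS-G the only factor named (Randomisation).

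**Assumptions**
- Allocation is 1:1. The ratio is not stated in words but follows naturally from two arms and blocks of four.
- Telemedicine follow-up is given in the intervention arm.

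**1. The plan's own figure.** The article gives no figure for the rural split. Its sample size, used in step 4, reproduces: n = 2(1.960 + 1.282)² × 15² / 7.8² = 77.7, so 78 per group.

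**2. Rural split as planned.** The number X of rural patients in the intervention arm is close to Binomial(10, 0.5):
- P(X = 5) = 252/1024 = 24.6%
- P(X ≤ 3) = (1 + 10 + 45 + 120)/1024 = 176/1024 = 17.2%
- P(X ≤ 2) = (1 + 10 + 45)/1024 = 56/1024 = 5.5%

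Two checks agree. A hypergeometric calculation (10 drawn from 204, 102 per arm) gives 16.6% for 3 or fewer and 5.0% for 2 or fewer. A simulation of blocks of four within two CIRS-G strata, with the share above the cut-off assumed to be 70%, 80% or 90%, gives 5.0% to 5.3% for 2 or fewer.

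**3. Rural split with a separate rural list in blocks of four.** Two full blocks give 4:4. The last two patients come from a third block: both go to the intervention with probability (2/4)(1/3) = 1/6, both to usual care with probability 1/6, and one to each with probability 4/6. So X is 4, 5 or 6 with probabilities 17%, 67% and 17%. Three or fewer cannot occur.

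**4. Effect on the primary comparison.** Suppose, generously, that rural patients differ from the rest by the full 7.8 points.
- A 7:3 split shifts the rural share between arms by 4/102 = 3.9 percentage points and the mean difference by 7.8 × 4/102 = 0.31 points.
- An 8:2 split shifts the mean difference by 7.8 × 6/102 = 0.46 points.
- The standard error of the difference is 15 × √(2/78) = 2.4 points.

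The larger shift is about a fifth of one standard error (0.46/2.4 = 0.19).

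**5. What balance buys for feasibility.** If follow-up succeeds in every telemedicine patient, the exact 95% lower limit for the success proportion is 0.025^(1/n): 29% for 3 of 3, 40% for 4 of 4 and 48% for 5 of 5.

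**The case against.** The case against acting is that this is a preference, not an error. Randomising a 10-patient subgroup without its own stratum is valid, the article gives a reason for choosing CIRS-G, and telemedicine feasibility is not among the listed primary or secondary aims or the hypotheses. Even perfect balance yields five telemedicine patients, and step 5 shows how little five can establish. All of this stands. It limits the weight of the point but does not answer it: a feasibility test is announced, and its size is left to avoidable chance.

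Four stronger readings are tempting, and the article does not support them.

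- **That rural imbalance threatens the main result.** The rural group is 10 of 204 (4.9%), and step 4 shows a negligible shift, already covered by the standard error.
- **That the feasibility risk is one in three.** The chance of a 7:3 or worse split in either direction is 2 × 17.2% = 34.4%, but half of those outcomes give more telemedicine patients, not fewer. The two-sided figure is relevant only to the rural-metropolitan comparison, and then only if treatment effects are compared.
- **That the trial should be stratified by clinic.** The article does say "The trial will be completed in two outpatient clinics", one of them regional, but all patients come from one intensive care unit, and nowhere does it say that the rural telemedicine patients are those seen at the regional clinic.
- **That the article restricts telemedicine to the intervention arm.** It does not say so outright. This is an inference, though a natural one, from the screening and referral described alongside it.

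**Conclusion.** The point holds as a cheap improvement. With CIRS-G as the only factor, there is about a 17% chance that 3 or fewer of 10 rural patients are allocated to telemedicine follow-up, and a 5.5% chance of 2 or fewer. A separate blocked list reduces both to zero. This rests on 1:1 allocation, on 10 rural patients being enrolled, on telemedicine belonging to the intervention arm, and on CIRS-G being the only factor because it is the only one named, twice.

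The benefit is confined to the descriptive feasibility test and the rural-metropolitan comparison. A reader might infer that the primary analysis is compromised, or that stratifying would make the rural subgroup informative; neither follows. The limit on what the subgroup can show is its size, which the change leaves as it is.

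**What to change.** Allocate rural patients from one separate envelope list in blocks of four, and include rural residence as a covariate in the models. Define the factor as rural residence, not clinic site. Patients are randomised just before hospital discharge, so where they are going should be known when the envelope is drawn.

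The cost is one extra set of envelopes and a one-line amendment, with no added patients. The downsides are one incompletely filled block in a small stratum and, with a single rural list, no CIRS-G stratification for these 10 patients. If CIRS-G is to be kept for them, two rural lists crossed with it still hold the count at 4 to 6. With 10 patients in two lists, the numbers left over after full blocks can only be 0 and 2, 1 and 1, or 3 and 3, and each gives an arm difference of at most 2.

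The change should be made before the first allocation. Made later, it protects only the rural patients still to be enrolled.
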